## Methods

### Study Design

The Sentinel study is an observational, exploratory, monocentric pilot implementation study with a pretest-posttest evaluation design and an overall duration of 24 months. The project does not introduce an experimental clinical treatment and does not modify the legal or clinical duties of professionals involved in suspected child maltreatment. Rather, it evaluates the implementation of 2 organizational tools: a secure digital registry for standardized documentation and a structured training program for pediatric health care professionals. The primary objective is to assess registry usability and feasibility. Secondary objectives are to evaluate training effectiveness, reporting completeness, reporting timeliness, and preliminary changes in suspected maltreatment reporting rates before and after implementation.

The project is organized into 2 interconnected components: the registry component and the training component. These components will be implemented sequentially and then evaluated jointly because the registry is intended to standardize documentation, whereas training is intended to improve recognition, case management confidence, and appropriate use of the registry.

The operational sequence will include development and internal testing of the REDCap registry; definition of the minimum dataset and reporting workflow; recruitment of hospital and community pediatric professionals; baseline assessment of knowledge, competencies, and reporting activity; delivery of the training program; activation of registry data entry; continuous monitoring of registry completeness and technical issues; follow-up assessment of outcomes; statistical analysis; and dissemination of results. All activities will be coordinated by an internal scientific committee responsible for methodological quality, ethical compliance, data protection procedures, and adherence to project timelines.

Because of its observational and pilot implementation nature, the study will not interfere with clinical decision-making, child protection duties, or mandatory reporting obligations. Professionals will continue to follow existing institutional and legal procedures for suspected maltreatment. Study data will be used only to evaluate registry use, reporting activity, and educational outcomes and identify preliminary indicators of feasibility, usability, acceptability, and implementation impact that can inform future multicenter or regional surveillance models.

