### Participants and Recruitment

The study population will consist of health care professionals from the regional pediatric network, including hospital and community pediatricians, pediatric residents, nurses, psychologists, and other professionals involved in the recognition, documentation, or management of suspected child maltreatment according to local organizational arrangements.

Recruitment will occur through institutional invitations circulated within the hospital-community pediatric network. Participation will be voluntary and require written informed consent. Eligible participants will be professionals aged 18 years or older who work in pediatric or child health settings, attend the training program, and agree to complete the evaluation questionnaires. Participants will be asked to complete baseline and posttraining assessments and, where applicable, use the registry during the implementation period.

Exclusion criteria will comprise refusal or withdrawal of consent, failure to complete the training program, nonparticipation in the practical registry sessions, or missing primary outcome data for the relevant analysis. A minimum of 30 professionals will be targeted. This sample is considered appropriate for a pilot feasibility study and for preliminary estimation of usability, training gains, and reporting process indicators.

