#### Training Component

Training is a strategic component of the project and is designed as an integrated educational intervention with theoretical, practical, and supervised components. Its purpose is to improve recognition of suspected maltreatment, appropriate documentation, awareness of legal and ethical responsibilities, confidence in multidisciplinary communication, and correct use of the REDCap registry.

The theoretical phase will include in-person lectures and e-learning modules. Training content will cover definitions and typologies of maltreatment, clinical warning signs, differential diagnoses, trauma-informed communication with children and families, documentation standards, legal and institutional reporting pathways, interprofessional coordination, data protection, and correct use of the digital registry.

The practical phase will include online and interactive webinars; hands-on sessions on data entry into the registry; and small-group supervision sessions led by experts in pediatrics, psychology, and forensic medicine. The effectiveness of the training will be evaluated using a pretest-posttest repeated-measure design. Each participant will complete a knowledge and competency assessment questionnaire before and after the training. The questionnaire will include multiple-choice questions and clinical scenarios aimed at measuring participants’ ability to recognize indicators of abuse, activate appropriate reporting pathways, and use the digital tool effectively.

Participants’ satisfaction, perceived usefulness, confidence, and perceived transferability to clinical practice will be assessed after training using 5-point Likert-scale items and open-ended questions. Results will be summarized using descriptive statistics and complemented with thematic qualitative analysis of open-ended responses to identify perceived strengths, implementation barriers, training needs, and suggestions for improvement.

Exploratory multivariable analyses will identify predictors of training gain, satisfaction, registry usability, and active registry use considering age, professional role, years of experience, work setting, previous child protection training, and frequency of registry use.

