### Outcomes and Measurement Time Points

The primary outcome is registry usability, measured using the mean SUS score collected after participants use the registry. Specifically, the SUS will be administered once at the end of the 12-month registry activation and follow-up period or earlier for participants who discontinue participation after having completed the minimum required registry exposure. Eligible respondents will be trained and authorized hospital or community professionals involved in suspected maltreatment recognition, documentation, or case management. To ensure that SUS responses reflect actual exposure to the tool, participants will be included in the primary SUS analysis only if they have entered at least one registry record or completed at least one supervised registry use session or simulation. Participants without any registry exposure will not contribute to the primary SUS analysis.

Secondary outcomes include feasibility indicators (active users, number of records, completion of mandatory fields, technical support requests, and time to complete a report), training outcomes (pretest-posttest knowledge and competency scores, satisfaction, and qualitative feedback), and reporting outcomes (number and rate of suspected maltreatment reports, reporting timeliness, duplicate reports, follow-up documentation, and activation of child protection pathways). Baseline data will be collected before training and registry activation, posttraining outcomes will be collected immediately after training, and registry usability and implementation outcomes will be collected during registry use and at the end of the observation period.

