Associations between participant characteristics and outcomes will be explored using multivariable linear, logistic, or count regression models according to the distribution and nature of the dependent variable. Candidate predictors will include professional role, years of experience, work setting, previous child protection training, participation in practical sessions, and frequency of registry use. All analyses will be 2 tailed, with a significance level set at *P*<.05.

Missing data will be described by variable and time point. Complete-case analysis will be used for the primary pilot analyses. If the proportion and pattern of missing data justify it, multiple imputation or sensitivity analyses will be performed. Qualitative responses will be analyzed thematically by grouping open-text answers into recurrent categories related to usability, workflow integration, training usefulness, barriers, and facilitators.

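### Two candidate predictors in the exploratory models conflict with the study design: registry-use frequency comes after the training outcomes, and practical-session participation hardly varies once the exclusions are applied

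*Protocol article*

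**What the plan says.** All references are to the protocol article.

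- **Outcomes of the models.** Training Component says that exploratory multivariable analyses will look for "predictors of training gain, satisfaction, registry usability, and active registry use".
- **First predictor list.** The same sentence continues: "considering age, professional role, years of experience, work setting, previous child protection training, and frequency of registry use".
- **Second predictor list.** Statistical Analysis, Overview: "Candidate predictors will include professional role, years of experience, work setting, previous child protection training, participation in practical sessions, and frequency of registry use". The two variables at issue are the last two, "participation in practical sessions, and frequency of registry use".
- **Exclusions.** Participants and Recruitment excludes people for "nonparticipation in the practical registry sessions", and also those who do not complete the training.
- **Timing.** Study Design gives the order as "delivery of the training program; activation of registry data entry". Study Setting and Timeline allots 3 months to training and then 12 months to registry activation and follow-up. Outcomes and Measurement Time Points says that "posttraining outcomes will be collected immediately after training", and places the SUS at the end of the 12 months, or earlier for people who leave after enough exposure.
- **Numbers.** Sample Size Calculation plans for 25 to 30 professionals; Participants and Recruitment targets at least 30. The overview uses complete cases for the primary pilot analyses and a 5% two-sided level throughout.

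The article does not say which predictors go with which outcomes.

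**The concern.** A predictor has to vary among the people analysed, be distinct from the outcome, and be fixed before the outcome. Read literally, the two lists break each condition at least once.

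If the text is followed, a regression of training gain on later registry use will be reported as if use predicted gain, when the plausible direction is the reverse. A regression of active use on frequency of use will show a strong association that is built in by definition. A yes/no participation term will either drop out of the software's fit or rest on very few people. The overview places these models under the same significance level as everything else, and the article describes the study's results as effect-size estimates for future multicenter work. Associations of this kind should not be carried forward as predictors.

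**Working it through.** **1. Time order of frequency of registry use.** Set against the schedule:

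| Outcome of the model | When measured | When registry use accrues | Order |
|---|---|---|---|
| Training gain | Immediately after training | 12 months after activation | Predictor after outcome |
| Satisfaction | After training | 12 months after activation | Predictor after outcome |
| Active registry use | During registry use | Same 12 months | Overlaps the outcome |
| SUS | End of the 12 months, or earlier at discontinuation | Before the SUS | Sound |

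One of the four pairings is correctly ordered, two run backwards, and one relates a behavior to another measure of the same behavior.

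**2. Participation in practical sessions.** Training Component puts the practical phase inside the training: webinars, hands-on registry sessions and small-group supervision. People who miss the registry sessions, or who do not complete training, are excluded. With a yes/no coding, the column is 1 for everyone, or nearly everyone, analysed. A column of ones duplicates the intercept, so its coefficient cannot be estimated. If a few people attended the registry sessions but missed another element and still counted as completers, the coefficient would rest on those few.

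**3. The two lists.** Four variables are common besides frequency: role, experience, setting and previous training. Age is only in Training Component; practical-session participation is only in the overview. Each list has six variables.

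**4. Size of a full model.** The article gives no coefficient count or sample size for these models, so there is no stated figure to reproduce. Assumptions: role has L levels, each of the other five variables takes one coefficient, and all candidates enter together.

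Coefficients p = (L − 1) + 5. With no true association, expected R-squared = p/(n − 1), and residual degrees of freedom = n − p − 1.

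| Role levels | p | n = 25: R-squared, df | n = 30: R-squared, df |
|---|---|---|---|
| 2 | 6 | 6/24 = 0.25, 18 | 6/29 = 0.21, 23 |
| 5 | 9 | 9/24 = 0.38, 15 | 9/29 = 0.31, 20 |
| 6 | 10 | 10/24 = 0.42, 14 | 10/29 = 0.34, 19 |

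If the participation term drops out of the overview's list as a constant, p falls by one for that list. The Training Component list has age in its place and keeps the full count.

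**5. After the change.** For outcomes other than the SUS, role, experience, setting and previous training remain, so p = (L − 1) + 3. With two role levels p = 4, and the expected null R-squared is 4/24 = 0.17 to 4/29 = 0.14. With five levels p = 7, giving 7/24 = 0.29 to 7/29 = 0.24. Age, if kept, adds one coefficient.

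**The case against.** The strongest reply is that the analyses are labelled exploratory, the predictors are only candidates, and the article says the pilot's results are mainly feasibility and effect-size estimates. Coding, number of terms and matching of predictors to outcomes are commonly left to an analysis plan that is not shown. This stands against any firm claim of overfitting. It does not answer the timing fault: the outcomes, the predictor and the schedule are all stated here, and they do not fit together.

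On participation, the exclusion concerns the registry sessions, while the practical phase is wider; completing training is not defined as full attendance; and the SUS rules themselves allow for people with no registry exposure. A count of sessions attended could vary. This stands. A reader might infer that no coefficient can exist for this variable, but that follows only for a yes/no coding with no exceptions.

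Active registry use is not defined, so it is not shown to be identical to frequency of use. That also stands; essentially circular is as far as the text supports. Frequency of registry use is not defined either. It might be read as practice entries during training, which would precede the posttest, but the article never says so.

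A reader might also count three faulty variables. There are two: being circular and coming too late are faults of the same variable in different models.

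**Conclusion.** The point holds for two variables. Frequency of registry use is misplaced in the models for training gain, satisfaction and active use, and sound for the SUS. This rests on reading it as use of the live registry. Participation in practical sessions is uninformative, or nearly so, if coded yes/no. The two lists disagree and need to be reconciled.

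The model-size arithmetic is a caution. It assumes that all candidates enter one model and that role has 2 to 6 levels; across that range there are 6 to 10 coefficients and an expected null R-squared of about 0.21 to 0.42 at 25 to 30 people. A reader might fix on nine coefficients, or multiply false-positive risks across the four outcomes. The article states neither the role coding nor that every candidate enters every model, and outcomes measured on the same people cannot be taken as independent.

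Nor does this undermine the main results. The primary SUS analysis, the paired pretest-posttest comparison and the reporting-rate model use none of these predictors. It is a correction to exploratory secondary models.

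**What to change.** 1. Use frequency of registry use only in the SUS model, counted up to the date of each participant's SUS. Remove it from the models for training gain, satisfaction and active registry use.
2. Delete participation in practical sessions, or replace it with the number of sessions attended, provided that attendance is recorded and varies.
3. Give one list of pre-training predictors in both Training Component and the Statistical Analysis overview, and decide there whether age is included.
4. As a precaution, keep the models small, for example by grouping role into few levels, and report estimates with 95% CIs as exploratory.

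The cost is wording, plus an attendance record if the session count is chosen, and fewer exploratory associations to report. Under Ethical Considerations, a protocol modification goes to the ethics committee and the registration is updated. The Results section says that data analysis has not started, so the change can still be made before results are seen.

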#### Sample Size Calculation

The sample size was determined to ensure adequate statistical power for detecting meaningful effects in both the usability and training evaluations. Assuming a medium effect size (Cohen *d*=0.5) for the improvement in knowledge and competency scores between pre- and posttraining assessments, a paired-sample *t* test with an α level of .05 and power (1 – β) of 0.80 requires a minimum of 27 participants.

This estimate aligns with the planned recruitment target of 25 to 30 professionals, which is considered sufficient to assess feasibility, usability, and preliminary impact within this exploratory pilot phase. For the SUS usability analysis, a sample of 25 participants allows for the estimation of the mean score with a 95% CI width of ±5 points, which is consistent with published methodological recommendations for usability testing in health care settings. Because this is a monocentric pilot study, analyses will be interpreted primarily as estimates of feasibility and effect size for future multicenter studies rather than as definitive evidence of effectiveness.

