### Statistical Analysis

#### Overview

Quantitative analyses will be performed using recognized statistical software, such as SPSS, R, or Stata. Descriptive statistics will be calculated for all study variables. Continuous variables will be summarized as means and SDs or medians and IQRs according to distribution. Categorical variables will be summarized as frequencies and percentages. All estimates will be reported with 95% CIs when appropriate.

Pretest-posttest comparisons of knowledge and competency scores will be performed using 2-tailed paired-sample *t* tests when normality assumptions are met, as assessed using the Shapiro-Wilk test and visual inspection of distributions. When assumptions are not met, Wilcoxon signed-rank tests will be used. Mean change scores, standardized effect sizes, and 95% CIs will be reported to support interpretation of training effectiveness.

Registry usability will be evaluated by calculating the mean SUS score and comparing it with established interpretive benchmarks, where scores of 70 or higher are considered acceptable and scores of 80 or higher indicate excellent usability [44]. A 1-sample *t* test or Wilcoxon signed-rank test will be used to compare observed SUS scores with the prespecified benchmark depending on distributional characteristics.

Changes in reporting rates of suspected child maltreatment before and after implementation will be analyzed using Poisson regression models, estimating incidence rate ratios with 95% CIs. The primary pretest-posttest comparison will use reports per professional month as the operational denominator. When service volume data are available, additional models will use the number of pediatric consultations or contacts as an offset to estimate reports per 1000 contacts. Overdispersion will be assessed by comparing the deviance and Pearson chi-square statistics with the df; if overdispersion is present, negative binomial regression or robust SEs will be applied. Repeated reports and potential duplicates will be described separately and, in sensitivity analyses, excluded or counted once per suspected case according to the predefined duplicate management rules.

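### The minimum of 27 matches a one-sided calculation; the 2-tailed paired t test in the plan needs 34, so 25 to 30 participants give 67–75% power, not 80%

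*Protocol article*

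**What the plan says.** All of this is in the protocol article.

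- **Sample Size Calculation.** The section opens by presenting the sample as chosen to give adequate power for the usability and training evaluations. For the pre-to-post change in knowledge and competency scores it assumes Cohen d = 0.5 and a paired-sample t "test with an α level of .05 and power" "of 0.80 requires a minimum of 27 participants". It does not say whether the calculation is one- or two-sided. It then says the result fits the "planned recruitment target of 25 to 30 professionals".
- **Statistical Analysis, Overview.** "Pretest-posttest comparisons of knowledge and competency scores will be performed using 2-tailed paired-sample" t tests, with the Wilcoxon signed-rank test as fallback. Later in the same section: "All analyses will be 2 tailed, with a significance level set at" P<.05. The primary analyses use complete cases.
- **Participants and Recruitment.** "A minimum of 30 professionals will be targeted". Professionals who withdraw, do not finish the training, miss the practical registry sessions or lack the relevant outcome data are excluded.

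**The concern.** Twenty-seven is low for a two-sided paired t test at d = 0.5 with 80% power. It suggests that the number was computed for a one-sided test while the analysis is fixed as two-sided. If so, the study lacks the power it claims for the only hypothesis test that is given a power calculation (the System Usability Scale figure is a confidence-interval width). A non-significant training result would then be taken as stronger evidence of no gain than it is, because the true type II error is above the stated 20%.

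The two recruitment statements add to the problem. At least 30 and 25 to 30 are different targets, and a sample of 25 would miss even the stated minimum of 27.

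**Working it through.** **Inputs.** d = 0.5, alpha = .05 and power = 0.80 come from Sample Size Calculation. Two-sided testing comes from the Statistical Analysis overview. Planned sizes of 25 to 30 and at least 30 come from Sample Size Calculation and from Participants and Recruitment. No pre-post correlation or separate SD is given, so d is taken as the mean change divided by the SD of the changes, the scale on which a paired t test works.

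**Method.** Exact power comes from the noncentral t distribution with n − 1 degrees of freedom and noncentrality d√n. The required n is the smallest with power of at least 0.80. Two approximations serve as a check: ((z_alpha + z_beta)/d)², and the same plus z_alpha²/2 as a small-sample correction.

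**Step 1: reproduce 27.** With one-sided alpha .05:

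- Normal approximation: ((1.645 + 0.842)/0.5)² = 24.7, so 25.
- Corrected: 24.73 + 1.645²/2 = 26.1, so 27.
- Exact: n = 26 gives 79.8% and n = 27 gives 81.2%, so 27.

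The one-sided calculation returns the stated figure exactly.

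**Step 2: the test in the plan.** With two-sided alpha .05:

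- Normal approximation: ((1.960 + 0.842)/0.5)² = 31.4, so 32.
- Corrected: 31.40 + 1.960²/2 = 33.3, so 34.
- Exact: n = 33 gives 79.5% and n = 34 gives 80.8%, so 34.

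Even the crudest two-sided formula gives 32, so rounding or choice of software does not explain 27.

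**Step 3: what the planned sizes deliver (two-sided).**

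| n | Noncentrality 0.5√n | Power at d = 0.5 | Type II error | d detectable with 80% power |
|---|---|---|---|---|
| 25 | 2.50 | 67.0% | 33.0% | 0.58 |
| 27 | 2.60 | 70.6% | 29.4% | 0.56 |
| 30 | 2.74 | 75.4% | 24.6% | 0.53 |
| 34 | 2.92 | 80.8% | 19.2% | just under 0.5 |

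**Step 4: losses (illustration).** The document gives no loss rate. If 15% of 30 were excluded, 30 × 0.85 = 25.5 would remain; power is 67.0% at 25 and 68.8% at 26.

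**Step 5: the fallback test.** Under normality the Wilcoxon test has efficiency 3/π relative to the t test, so 34/(3/π) = 35.6, about 36. On this definition of d, 34 is therefore a floor.

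**Step 6: another definition of d.** If d = 0.5 were on the raw-score SD scale, the effect on the change scale would be 0.5/√(2(1 − ρ)), where ρ is the pre-post correlation. Two-sided n would be:

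| ρ | Effect on change scale | n |
|---|---|---|
| 0.3 | 0.423 | 46 |
| 0.4 | 0.456 | 40 |
| 0.5 | 0.500 | 34 |
| 0.6 | 0.559 | 28 |
| 0.7 | 0.645 | 21 |

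**The case against.** The strongest reply is that the section states neither the sidedness of the calculation nor how d is standardised. On the raw-score scale, with a pre-post correlation of about 0.61, a two-sided test does need 27. That the authors ran a one-sided calculation is therefore an inference. This much stands. It does not rescue the sentence: no correlation is stated, values of 0.5 or below need 34 or more, and the one-sided result fits without any added assumption.

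The second reply is that little depends on it. Training scores are a secondary outcome, the study is an exploratory single-centre pilot, effect sizes with 95% CIs are promised, and the section itself says results will be read mainly as estimates. That limits the damage and is why more recruitment is not demanded. But the same section claims adequate power, and a power figure, once given, must be right for the named test.

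Third, 67% is the bottom of the range; at the other stated target, 30, the shortfall before losses is about 5 points (75.4% against 80%). That is correct, and it shows why a single target is needed.

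Fourth, the 15% loss has no source, and a condensed article may leave a loss allowance to the full protocol. Agreed: the scenario is only an illustration, and the conclusion does not depend on it.

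**Conclusion.** The point holds. For the 2-tailed paired t test in the plan, with d = 0.5, alpha .05 and 80% power, the minimum is 34, not 27, a shortfall of 7. With 25 to 30 evaluable participants power is 67% to 75%, and 80% power is reached only for effects of d = 0.58 to 0.53 or larger. This rests on one assumption, that d is standardised by the SD of the change scores. The one-sided origin of 27 is inferred from an exact match. Separately, and without any calculation, the two recruitment statements contradict each other, and the lower end of one is below the plan's own minimum. The primary usability outcome is not affected by this calculation.

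**What to change.** In Sample Size Calculation, replace the training sentence with wording such as:

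> A 2-tailed paired t test (alpha .05, d = 0.5 on the change-score scale) needs 34 participants for 80% power. With 25–30 evaluable participants power is 67–75%, and the smallest effect detectable with 80% power is d = 0.53–0.58.

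In addition:

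- State one recruitment target, identical in Participants and Recruitment and in Sample Size Calculation, and say how many evaluable participants are expected after exclusions. Narrow the power range above to match.
- Remove the claim that the sample gives adequate power, and the remark that the estimate fits the target. The usability part can rest on its own precision statement.
- Do not make the test one-sided to preserve 27; that would contradict the overview.

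The cost is protocol wording and a less favourable stated power. Enrolment need not rise if the pilot is presented as estimation; a sponsor who wants to keep the 80% claim would need 34 evaluable participants. The Results section reports that recruitment is under way and analysis has not begun, so the change can still be made through the amendment route described under Ethical Considerations.

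### The sample-size section equates recruited with analysed professionals, sets a recruitment range whose lower end is below its own minimum of 27, and conflicts with the target of at least 30 given elsewhere

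*Protocol article*

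**What the plan says.** The Sample Size Calculation section makes three statements. A paired t test with d = 0.5, α = .05 and power 0.80 needs at least 27 participants. Next, "This estimate aligns with the planned recruitment target of 25 to 30 professionals". For the primary outcome, "a sample of 25 participants allows for the estimation of the mean score with a 95% CI width of ±5 points". It gives no SUS standard deviation and no loss rate.

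Other sections separate the number recruited from the number analysed:

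- **Participants and Recruitment** excludes for refusal or withdrawal of consent, and for "failure to complete the training program, nonparticipation in the practical registry sessions, or missing primary outcome data for the relevant analysis". The same paragraph sets another target: "A minimum of 30 professionals will be targeted".
- **Outcomes and Measurement Time Points** says that "the SUS will be administered once at the end of the 12-month registry activation and follow-up period". It makes an exception for people who leave the study once they have met the minimum exposure: they fill it in sooner. People with no registry exposure do not enter the primary SUS analysis. Post-training scores are collected immediately after training.
- **Statistical Analysis, Overview** says "Complete-case analysis will be used for the primary pilot analyses". It then allows multiple imputation or sensitivity analyses if the missing data justify them. All tests are two-tailed.

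**The concern.** A requirement of 27 pairs and 25 SUS responses is a requirement on the analysed number. A target of 25 to 30 is a number recruited. The section says that the one aligns with the other, but the protocol's own exclusion and complete-case rules allow the two to differ.

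The mismatch does not depend on any assumed loss: the lower end of the range, 25, is already below 27. The two sections also disagree on the target, so a reader cannot tell whether 30 is the floor or the ceiling, and therefore whether there is any room for loss.

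At stake is whether the stated ±5 points and 0.80 power describe the data that the study will have. The study is a pilot meant to supply estimates for later multicentre work, so its stated precision is a main justification for its size.

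**Working it through.** **Inputs from the protocol.** Recruitment target 25 to 30 (Sample Size Calculation) or at least 30 (Participants and Recruitment); SUS half-width 5 at n = 25; d = 0.5, α = .05, power 0.80, n = 27 for training; two-tailed tests. **Assumed:** the loss rate. The SUS SD can only be back-solved.

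**Step 1: lower bound with no loss.** 25 recruits give at most 25 pairs, and 25 < 27.

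**Step 2: room for loss with 30 recruits.**
- SUS: (30 − 25)/30 = 16.7%.
- Training pairs: (30 − 27)/30 = 10%.

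With 25 recruits the room for loss is zero for SUS.

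**Step 3: analysed numbers under assumed loss.**

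| Assumed loss | From 25 | From 30 |
|---|---|---|
| 10% | 22.5 | 27 |
| 20% | 20 | 24 |

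**Step 4: SUS precision.** The ±5 cannot be verified independently because the SD is missing. Solving half-width = t(0.975, n − 1) × SD/√n at n = 25 gives SD = 5 × 5/2.064 = 12.1 (12.8 with the normal quantile, 25/1.96). With SD 12.11 and the t quantile:

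| n analysed | Half-width |
|---|---|
| 20 | 5.67 |
| 22 | 5.37 |
| 24 | 5.11 |
| 25 | 5.00 |
| 27 | 4.79 |
| 30 | 4.52 |

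The SD matters more than the loss. At an assumed SD of 10, 18 responses give ±5 or better; at an assumed SD of 15, 38 are needed.

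**Step 5: training power.** Power comes from the noncentral t distribution with df = n − 1 and noncentrality 0.5√n. The stated 27 reproduces with a one-sided test (power 0.812). With the two-tailed tests that the protocol specifies, power is:

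| n pairs | Two-sided power |
|---|---|
| 20 | 0.56 |
| 24 | 0.65 |
| 25 | 0.67 |
| 27 | 0.71 |
| 30 | 0.75 |
| 34 | 0.81 |

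Sidedness is a separate issue. It matters here only because a restated power has to use the two-sided values.

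**The case against.** A reader might infer that the stated SUS precision fails unless nobody is lost between enrolment and the end of the 12-month registry period. The documents do not support that reading, for four reasons.

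- If the minimum of 30 is the true target, there is room for 16.7% loss before SUS responses fall below 25.
- Leaving the study does not by itself lose the SUS score. Those who discontinue after the minimum registry exposure complete it early, and one supervised session or simulation counts as exposure. The long interval also has no bearing on the training pairs, which are complete once training ends.
- The SD is back-solved so that n = 25 gives exactly 5.00, so any smaller n must exceed it. The protocol states ±5 in whole points, and 5.11 and 5.37 both round to 5.
- The cost is small: at 20 analysed the half-width grows by 5.67 − 5.00 = 0.67 points on a 100-point scale, and no decision hangs on the threshold.

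All four stand, and they limit the point. It can also be said that an article may leave a loss allowance to the full protocol. That is fair for a missing loss rate alone. It does not answer the stated claim that 25 to 30 aligns with 27, or the two conflicting targets. The early SUS does not ensure a score from people who never finish training, miss the practical sessions or do not respond.

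**Conclusion.** The point holds in a limited form. The Sample Size Calculation section uses recruited and analysed numbers interchangeably, its lower bound of 25 cannot deliver its own 27 pairs, and its range contradicts the minimum of 30 under Participants and Recruitment. These three statements need no assumption.

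The consequence for the primary outcome is modest: about ±5.1 to ±5.7 points at 24 to 20 analysed. That range rests on an SD of about 12.1 inferred from the protocol's own figure and on assumed loss, and the early SUS would recover some responses. The consequence for training is larger: two-sided power is about 0.56 to 0.75 for 20 to 30 analysed pairs, so the unqualified 0.80 is not reached anywhere in the stated range. Part of that gap comes from sidedness and not from loss.

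**What to change.** 1. State one recruitment target and use it in both Participants and Recruitment and Sample Size Calculation.
2. Label 25 (SUS) and 27 (training pairs) as analysed numbers.
3. State an assumed loss rate, with its basis, and the SUS SD behind ±5.
4. Restate the SUS half-width and the two-sided training power at the expected analysed number, in place of the unqualified ±5 and 0.80. For illustration, if the target is 30 and 20% loss is assumed: 24 analysed, about ±5.1 points at an SD of 12.1, and power about 0.65 at d = 0.5.

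The cost is wording, plus stated figures that are less favourable. No extra recruitment is needed if the sponsor accepts the restated power, which fits the section's own position that results are estimates for later studies. Keeping a claim of 0.80 two-sided power at d = 0.5 would need 34 analysed pairs, more than the 25 to 30 range can supply. Data analysis has not started, so the text can be corrected before any result is known.
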